## Abstract

**Background:**

Suicide is a recognized global public health problem that continues to pose substantial challenges in the United States. Veterans and service members are particularly at risk. Caring Contacts is a simple, scalable intervention comprising brief, periodic messages sent over 1 to 2 years that express unconditional care and concern. It reduces suicide risk among individuals with recent suicidal ideation or attempts and has demonstrated acceptability in military and veteran samples, but little is known about the mechanisms of Caring Contacts or its applicability to populations who are not suicidal.

**Objective:**

We aim to evaluate if receiving Caring Contacts reduces suicide risk among veterans and active service members recruited based on their stress or distress levels, using ecological momentary assessment (EMA) and survey measures of suicidal ideation and cognitions; to examine the experiences of diverse veterans and service members with Caring Contacts; to evaluate if receiving Caring Contacts reduces distress (depression, substance use consequences, hopelessness, defeat, and psychological pain); and to identify the potential mechanisms of action for Caring Contacts (mattering, connectedness, social responsibility, and entrapment). Using EMA, this study will be the first to investigate mechanisms of the Caring Contacts intervention both in real time, as the messages are received, and over the course of 1 year.

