Furthermore, EMA-based models have demonstrated strong predictive accuracy for near-term suicidal thoughts and posthospital suicide attempts [31,32], highlighting the utility of self-reported data and real-time monitoring in guiding risk assessment and intervention delivery. As such, using EMA to study time-varying changes in suicide risk and related proximal risk factors has been a priority for the advancement of suicide research [43,46]. However, EMA has been underused to study suicide risk in veterans and service members despite its feasibility [47] and potential for increasing understanding of mental health problems [48]. By using EMA as our primary outcome measure, we will explore how Caring Contacts influences proximal risk factors and mechanisms of change in veterans and active-duty service members, both when individual messages are received and across the year-long intervention period. To control for the potentially confounding impact of frequent EMA and the study intervention, 3 conditions are used to study Caring Contacts both with and without monthly EMA.

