#### Potential Mechanisms of Caring Contacts (Aim 4)

To evaluate how Caring Contacts influence connectedness, we selected 4 mechanisms for testing based on prominent psychological suicide theories [40,89,90]: burdensomeness, entrapment, mattering, and personal and social responsibility. Measures of these possible mechanisms of action for the Caring Contacts intervention are administered through EMA and the baseline and follow-up surveys.

Two of the potential mechanisms, perceived burdensomeness and entrapment, are each assessed with a single question selected based on prior EMA studies studying suicide.

Perceived burdensomeness has consistently emerged as a robust predictor of SI, reflecting the harmful impact of feeling like a burden to others. During the EMA period, it is assessed using a slightly modified version of an item from the Interpersonal Needs Questionnaire [91] (“I felt that I was a burden to other people, or that they would be better off without me”), which has been used in previous EMA research [92].

Entrapment is a key construct in the integrated motivational-volitional model [40] of suicide and represents the psychological state of feeling trapped with no escape, which is strongly associated with suicidal intent. In this study, it is assessed at baseline and follow-up using the 16-item Entrapment Scale [76,77]. Items are scored on a 5-point Likert scale from 0 (“not at all like me”) to 4 (“extremely like me”) and include “I am in a situation I feel trapped in” and “I would like to get away from who I am and start again.” During the EMA period, it is assessed using a single item from the scale (“I feel trapped”). Higher scores indicate increased feelings of being trapped. The measure’s authors found it to be basically unidimensional and psychometrically valid [77].

A planned missingness design was implemented to reduce the length of each individual EMA, thereby lowering the effort needed by participants to complete it. Thus, 3 of the mechanisms that are measured with multiple items—mattering, personal responsibility, and social responsibility—are assessed in a random rotation at each of the 3 EMA points within a day.

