Mattering is how an individual perceives their significance and importance to others, which directly counters feelings of insignificance and isolation. In this study, it is measured using the 5-item General Mattering Scale [93-96] at baseline, follow-up, and in the EMA. Items are scored on a 4-point Likert scale from 1 (“not at all”) to 4 (“a lot”) and include “How much do other people depend on you?” and “How important do you feel you are to other people?” Higher scores indicate increased feelings of mattering to others. In contrast to mattering, antimattering is the extent to which an individual feels insignificant or worthless. It is valuable to assess both mattering and antimattering as it has been postulated that these constructs are not opposites of each other but rather capture distinct protective and risk factors [97-99]. The 5-item Anti-Mattering Scale is administered with the General Mattering Scale at baseline and follow-up. Items are scored on a 4-point Likert scale from 1 (“not at all”) to 4 (“a lot”) and include “How much do you feel like you don’t matter?” and “To what extent have you been made to feel like you are invisible?” Higher scores indicate greater feelings of antimattering.

In this trial, personal and social responsibility are defined as an individual’s feeling of accountability toward their own well-being and the well-being of others. They speak to an individual’s sense of belonging within broader social systems and reinforce protective roles within their network. In this study, they are measured by the two 4-item subscales of the 8-item Responsibility Scale [100] at baseline, follow-up, and during the EMA period. Items are scored on a 5-point Likert scale from 1 (“strongly disagree”) to 5 (“strongly agree”). Items from the personal responsibility scale include “I discipline myself to make the best use of my time doing meaningful things” and “I am conscientious in whatever I do, big or small.” Items from the social responsibility scale include “I am morally accountable for how I treat others” and “I am responsible to do my part to make the world a better place.” Higher scores indicate a greater sense of personal and social responsibility [100].

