For those participants who will complete EMA for all 12 months (n=340), we will conduct an *exploratory analysis* of changes over time in the mean and intraindividual SD of suicide outcomes. The unique and intensive sampling approach of EMA allows for fine-grained exploration of if and when outcomes change in a clinical trial. Specifically, we will first visually examine trajectories by condition to determine the shape of change *trajectories* over time. Then, following the determination of the shape, we will conduct a linear mixed effects growth model (eg, linear, nonlinear quadratic, and piecewise) [126-129], including a dummy-coded condition variable (with EMA only as the reference) as a predictor of both intercept and slope to determine how intervention condition impacts change in suicide outcomes over time.

For aims 1.2 and 3, to examine secondary suicide outcomes and measures of psychological distress, we will use analysis of covariance to examine condition-specific differences in continuous scores of suicide ideation and cognitions and examine group differences at 12 months, controlling for baseline values of the outcome variable of interest. Similarly, preplanned post hoc comparisons will compare (1) any Caring Contacts (combined) to no Caring Contacts, (2) Caring Contacts with and without EMA, and (3) EMA with and without Caring Contacts. For both aims 1.1 and 1.2, any baseline variables that were not successfully randomized will be included as covariates in the regression models.

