For aim 4, to examine potential mechanisms of Caring Contacts, we will use the within-EMA period data and examine within-participants mediation using dynamic structural equation modeling (with random intercepts and slopes) [130]. Dynamic structural equation modeling allows for the simultaneous estimation of within- and between-person effects that allow for idiographic mechanistic models over time, which can be ideal for answering questions about within-participant mechanisms of suicide outcomes. In line with recommendations for intensive longitudinal data analysis, all hypothesized mechanism variables (ie, mattering, personal and social responsibility, perceived burdensomeness, and entrapment) will be centered at both the between-person and within-person mean level. Then, within-person regression models will be run to examine the relationship between the hypothesized mechanisms and suicide outcome, using a lag-1 model and autoregressive covariance structure to account for assessments closer in time to be more highly correlated. Next, to examine the mediation effect of treatment condition on outcomes through the hypothesized mechanisms, we will estimate within-level indirect mediation effects, calculated as the product of the within-level effect of treatment condition on the mechanism (a path) and the effect of the mechanism on the suicide outcome. All mediation analyses will be examined at the within-person level (1-1-1), excluding cross-level mediation. Random starts will be used for all models to replicate the best log-likelihood. Finally, to examine the immediate versus delayed impact of the timing of Caring Contacts intervention, we will use autoregressive modeling to examine the direct impact on stress, distress, and suicide outcomes immediately following a Caring Contacts message compared to times without a message, using the EMA data. For all regressions, 95% CIs will be reported, and statistical significance will be set at *P*<.05.

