## Discussion

### Significance

This innovative trial will be the first RCT to examine (1) the impact of the Caring Contacts intervention on a broad population experiencing stress or distress and (2) the mechanisms of Caring Contacts, both when each message is received and during the course of the 1-year intervention. By recruiting veterans and service members experiencing a wide variety of stressors and psychological distress, the sample is more generalizable to those served by veteran service organizations, primary care, and general behavioral health care. If Caring Contacts reduces the risk of suicide, improves psychological distress, or both, then the intervention could be scaled up to include individuals who do not endorse suicidality but have the potential to benefit. As veteran service organizations are not equipped to systematically assess suicidality or to provide an intervention specifically for this segment of their membership, positive results would support their implementation with any veteran experiencing stress or distress.

EMA provides a powerful tool for measuring the impact of Caring Contacts by enabling real-time data collection in participants’ natural environments. This approach minimizes recall bias and allows a detailed exploration of how the intervention affects participants immediately after receiving Caring Contacts and over the course of 1 year. Thus, EMA allows researchers to gain valuable insights into the mechanisms of action of the Caring Contacts intervention. This can address critical gaps in understanding and pave the way for improved, scalable strategies to prevent suicide.

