### Conclusions

To conclude, this innovative RCT is designed to evaluate the Caring Contacts intervention for veterans and service members experiencing stress or distress while simultaneously evaluating potential mechanisms through which this evidence-based intervention is working. The EMAs right before and after Caring Contacts messages are received, as well as the monthly EMA tracking changes in mechanisms and outcomes during the course of the 1-year intervention, offer one view, while qualitative interviews with study participants offer another view into the impact of Caring Contacts. This is also one of the first trials for suicide prevention that focuses on EMA as the primary outcome. Results from this project will further inform optimal implementation of Caring Contacts and provide crucial insights to address the urgent need for practical, scalable mental health solutions.

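### Mechanisms are promised over the 1-year intervention as well as around each message, but no planned inferential analysis can compare mechanism levels between arms over the year

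*Protocol article*

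**What the plan says.** The promise is made in four places of the protocol article:

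- Abstract, Objective: the study will "investigate mechanisms of the Caring Contacts intervention both in real time, as the messages are received, and over the course of 1 year". The sentence is framed as work done with EMA.
- Introduction, Background: proximal risk factors and mechanisms of change will be explored "both when individual messages are received and across the year-long intervention period".
- Discussion, Significance: among the trial's claimed firsts is examining "the mechanisms of Caring Contacts, both when each message is received and during the course of the 1-year intervention".
- Discussion, Conclusions: one view of how the intervention works comes from "monthly EMA tracking changes in mechanisms and outcomes during the course of the 1-year intervention".

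On measurement, the section on potential mechanisms (Aim 4) says the mechanism measures "are administered through EMA and the baseline and follow-up surveys". Burdensomeness, entrapment (one item), mattering, and personal and social responsibility are in the EMA. The full 16-item Entrapment Scale is used only in the surveys. So is anti-mattering: "The 5-item Anti-Mattering Scale is administered with the General Mattering Scale at baseline and follow-up".

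On analysis, the Analysis Plan says that in the two arms with EMA all year the exploratory growth analysis will model "changes over time in the mean and intraindividual SD of suicide outcomes". For aim 4, "we will use the within-EMA period data and examine within-participants mediation using dynamic structural equation modeling". The indirect effect is the product of two paths: condition to mechanism, taken at the within level, and mechanism to suicide outcome. All mediation is kept at 1-1-1, and cross-level mediation is excluded.

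**The concern.** A claim about how a 12-month intervention works over 12 months needs evidence that randomisation to it moved the mechanism over that time. Here that evidence would be a between-arm comparison of mattering, burdensomeness, entrapment or responsibility, either as monthly trajectories or at month 12. No listed model has a mechanism as the dependent variable in such a comparison.

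The trial could therefore show that entrapment precedes suicidal ratings within an EMA week and describe it as a mechanism of Caring Contacts, with no usable estimate of whether Caring Contacts changed entrapment. A within-person association between entrapment and later ratings could appear equally in the arm that gets no messages.

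**Working it through.** **1. Design counts.** These reproduce the article's figures and show what data exist.

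- Months 1 to 11: 11 × 7 days × 3 = 231 assessments, as stated. Over 12 months: 12 × 7 × 3 = 252, as stated.
- Participants with EMA in all months: 510 × 2/3 = 340, as stated, so 170 per arm.
- All three arms have the 14-day baseline EMA, the month-12 EMA and both surveys (Table 1 and EMA Study).

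The article gives no detectable effect for a between-arm mechanism comparison. The nearest figure is f² = 0.03 for aim 1.2. Solving the noncentral F for three groups, N = 510, α = 0.05 and power 0.95 gives f² = 0.0305, which agrees.

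**2. Planned inferential models against the year-long question.**

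| Model in the Analysis Plan | Dependent variable | Between-arm mechanism comparison? |
|---|---|---|
| Aim 1.1 ANCOVA at 12 months | EMA suicide indicators | No |
| Exploratory growth model, n=340 | Suicide outcomes | No |
| Aims 1.2 and 3 ANCOVA at 12 months | Ideation, cognitions, distress | No |
| Aim 4 mediation | Mechanism (a path) and suicide outcome, within person | See step 3 |
| Aim 4 message-timing model | Stress, distress, suicide outcomes | No |

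**3. Can the a path serve?** Let C_i be the arm of participant i. It is the same at every occasion t, so the within-person part is C_i − mean_t(C_i) = C_i − C_i = 0. Its variance is zero, and a within-level effect of arm is not identified. From the other side, a mechanism centred at the person's own mean averages zero for every participant, so its mean cannot differ by arm.

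A simulation confirms this with 340 participants, 252 occasions each, person and occasion SDs of 1, and a true between-arm shift of 0.5. The variance of within-centred condition was 0. The arm contrast in the person-centred mechanism was 0 to rounding. The arm contrast in uncentred values was 0.62, which is 0.5 plus chance: SE = √(2/170) = 0.108, so about 1.1 SE away. The randomised effect lies wholly at the between-person level.

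**4. What a between-arm test could detect.** For ANCOVA with n per arm and baseline correlation r, SE in SD units = √((1 − r²) × 2/n). The detectable difference at two-sided α = 0.05 and 80% power is (1.96 + 0.84) × SE = 2.80 × SE. The article also uses power 0.8 for aim 4. The values of r and the loss are assumptions; the article gives neither.

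| n per arm | r | SE | Detectable difference (SD) |
|---|---|---|---|
| 170 (no loss) | 0.5 | √(1.5/170) = 0.094 | 0.26 |
| 170 (no loss) | 0.7 | √(1.02/170) = 0.077 | 0.22 |
| 119 (30% loss) | 0.5 | √(1.5/119) = 0.112 | 0.31 |
| 119 (30% loss) | 0.7 | √(1.02/119) = 0.093 | 0.26 |

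With no gain from baseline and no loss: 2.80 × √(2/170) = 0.30 SD.

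**The case against.** **The plan names an effect of condition on the mechanism.** It does, so it would be wrong to say the question is never raised. But the level is stated and the cross-level alternative is ruled out, and at that level the effect does not exist (step 3). If condition were read instead as whether a message had just arrived, the path could be estimated. It would then answer the real-time half, not the year-long one.

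**Aim 4 is not confined to one week.** This stands. The EMA blocks run through months 1 to 12, the power section counts 252 assessments per participant, and the aim 4 text speaks of estimating within- and between-person effects together. A reader might infer that mechanism data after the first weeks go unused; the article does not support that. Pooling the year's blocks, however, supplies neither a time trend nor a 12-month contrast between arms, and no between-person effect of condition on a mechanism is specified.

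**The article condenses a fuller plan.** This carries weight for the survey scales. A reader might infer that they enter no analysis at all. That is too strong: the Analysis Plan promises descriptive statistics for all variables and a check of baseline differences, a fuller plan may name a model, and the Objective's promise is about EMA. It carries less weight for the main point, because the article itself fixes the level of the aim 4 model and names the outcomes of each 12-month model. A fuller plan could meet the promise only by going beyond or departing from that text.

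**It overlaps with how the mediation is specified.** Partly true. But correcting the level of the a path would still leave no mechanism trajectory and no 12-month mechanism contrast.

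**Conclusion.** The point holds. Four statements promise study of mechanisms over the year, and no planned inferential analysis can compare mechanism levels between arms over that year. The growth model and the 12-month ANCOVAs name other outcomes, and the aim 4 a path is set where the randomised effect is zero by construction.

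As a supporting point only, the survey-only mechanism scales (16-item Entrapment, Anti-Mattering) are named in no inferential analysis.

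The consequence is limited to interpretation of a secondary aim; the primary suicide-risk comparison is not affected. The zero within-level effect needs only that arm is fixed after randomisation. The detectable differences of 0.22 to 0.31 SD rest on 170 per arm, an assumed baseline correlation of 0.5 to 0.7 and assumed loss of 0 to 30%. They show that the missing comparison would be informative; they do not measure an error in the plan.

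**What to change.** In the Analysis Plan:

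1. **Exploratory growth paragraph:** add the monthly EMA means of each mechanism as outcomes of the same growth model (n=340), with condition predicting intercept and slope.
2. **Aim 4 paragraph:** add a 12-month ANCOVA for each mechanism, adjusted for its baseline value. Apply it to the month-12 EMA mean and, where one exists, to the survey scale (entrapment, mattering, anti-mattering, personal and social responsibility; no survey version of burdensomeness is described). Use the three preplanned contrasts, with EMA with versus without Caring Contacts as the main one, since both those arms have monthly EMA and differ only in the messages. Label the analyses secondary and report 95% CIs.

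Otherwise, withdraw the year-long mechanism claim from the Objective, Background, Significance and Conclusions.

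No new data are needed, and the article places analysis after data collection ends. The cost is more secondary tests: five EMA and five survey mechanism scores give ten main contrasts, so about 10 × 0.05 = 0.5 would be expected below 0.05 by chance if nothing moved. Hence the secondary label and the emphasis on intervals. Mattering and the two responsibility subscales rotate across the three daily prompts. If each appears once a day, a month-12 mean rests on at most 7 prompts rather than 21, so baseline correlations may be lower for those three.

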**Methods:**

In this randomized controlled trial, veterans or service members (N=510) experiencing stress or distress recruited via social media advertisements will be offered best available resources and randomized into 1 of 3 study conditions: 12 months of Caring Contacts and monthly EMA, 12 months of Caring Contacts without monthly EMA, or 12 months of monthly EMA alone. The individuals in the Caring Contacts conditions will receive 13 messages. A subset of participants from each condition will be asked to complete a qualitative interview after the 12-month follow-up about their study experience.

**Results:**

This trial was funded in October 2023; recruitment started in April 2024 and will conclude in May 2025. As of December 2024, we have enrolled 321 participants. Final quantitative data collection will be completed by July 2026, 2 months after the final 12-month follow-up date. Data from the qualitative interviews will be collected until September 2026. Data analysis will occur following data collection, and the results are expected to be published in winter 2027.

**Conclusions:**

This study will be the first randomized controlled trial evaluating the impact of Caring Contacts among service members and veterans who were not recruited based on suicidality. If effective, our findings will demonstrate that Caring Contacts is beneficial for reducing multiple forms of psychological distress and suicide risk. In addition, we will evaluate potential mechanisms explaining the effects of Caring Contacts and assess the utility of EMA as a primary measure of outcome in suicide research trials.

